Meta‐analytic evidence in the general population, and for those with chronic pain, suggests that on average guided interventions are more clinically efficacious than unguided interventions.^27^, ^28^ In contrast, unguided models have greater public health potential, as they cost less, are easier to implement in routine care settings, and have been found to be efficacious for mild/subthreshold depression.^28^ Yet, participants with severe or complex mental health presentations, such as those with neurological comorbidities including epilepsy, may not achieve good clinical outcomes without clinician support.

Thus, the comparative clinical and cost‐effectiveness of guided and unguided digital interventions remains an important topical area of investigation^15^ and critical information to inform healthcare service providers. Reflecting this, a carefully developed digital chronic pain management intervention was similarly clinically efficacious and acceptable in an unguided and guided model; however, the unguided model was more cost‐effective.^29^ This research highlights the importance of comparative effectiveness trials to inform decision‐makers about the relative merits of different models of care. One recent randomized controlled trial (RCT) in adults with MS compared the efficacy of a digital cognitive behavior‐based program in a guided or unguided format with a treatment‐as‐usual, waitlist, control group.^22^ Both versions of the program led to a significant reduction in depression symptoms compared to the control group. However, a direct comparison between the guided and unguided groups was not performed. To date, there have been two RCTs of digital psychological interventions in epilepsy, both of which utilized unguided models of care.^24^, ^25^ Notably, while both reported that the treatment arms experienced significant improvements in symptoms of depression compared to controls, they also experienced relatively high dropout rates (>25%). On the other hand, an open trial of a guided digital psychological intervention to improve mental health in PWE observed very low rates of attrition (4%).^30^ These findings highlight potential differences in intervention engagement based on levels of guidance. However, conclusions in this area can only be reached following clinical trials that directly compare these different care models.

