### Participant eligibility

2.3

Eligible participants will have a confirmed diagnosis of epilepsy, self‐report experiencing difficulties with their emotional health, be aged 18 years or over, and currently living in Australia.

Exclusion criteria include those who are imminently suicidal or unable to keep themselves safe, those experiencing severe cognitive difficulties with day‐to‐day memory, attention, and ability to learn basic information, those who are unable to read and understand English, or those who do not have access to the internet.

Non‐eligible applicants will be notified and strongly encouraged to speak to their primary health professional to identify local treatment options available to them. They may also be directed to the MindSpot Clinic (www.mindspot.org.au), which offers a variety of similar courses for free to all adults within Australia. A suicide risk assessment will be conducted for all participants and appropriate triaging to external community and crisis services where appropriate.

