#### Primary outcomes

2.7.3

Patient Health Questionnaire 9‐Item (PHQ‐9). This is a measure of the number and severity of symptoms of depression, based on the DSM‐IV criteria for major depressive disorder.^34^
Generalized Anxiety Disorder 7‐Item (GAD‐7). This is a measure of symptoms of anxiety, based on the DSM‐IV criteria for GAD, but is sensitive to five different anxiety disorders.^35^

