### Clinical significance

3.2

Clinical significance will be reported in several ways. Consistent with previous research,^32^ we will calculate the average percentage improvement (e.g. pre‐treatment mean score – post‐treatment mean score/pre‐treatment mean score) for each group from pre‐treatment to post‐treatment and 3‐ and 12‐month follow‐ups, for the clinical outcomes, using the estimated marginal means from the GEE models. Second, the proportion of participants achieving a clinical improvement (defined as ≥25%) and large clinical improvement (defined as ≥50%) on the primary outcomes will be calculated and compared between groups using generalized linear models using appropriate statistical models (e.g., GEE). In addition, deterioration (i.e., symptom increase at post‐treatment of ≥30% and within the clinical range) will be compared between groups. Based on these outcomes, the number needed to treat (NNT) will be calculated. Finally, Hedges *g* effect sizes will be calculated for the between‐group and within‐group effects.

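### The deterioration rule (a rise of at least 30% from own baseline) cannot be met by participants who start above about 77% of the scale maximum, so they count as certain non-events

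*Protocol article*

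**What the plan says.** Section 3.2 (Clinical significance) of the protocol article sets two improvement thresholds, at 25% and 50%, and one worsening threshold. On improvement, "large clinical improvement (defined as ≥50%) on the primary outcomes will be calculated and compared between groups". The next sentence adds that "deterioration (i.e., symptom increase at post‐treatment of ≥30% and within the clinical range) will be compared between groups". It does not name the outcomes again, so I read it as applying to the same primary outcomes, PHQ-9 and GAD-7. The section then says that a number needed to treat will be derived from these outcomes.

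The rule has two conditions, both required: a relative rise of at least 30%, and a score in the clinical range. The section makes no provision for participants who start near the top of a scale.

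Section 2.3 (Participant eligibility) asks that participants "self‐report experiencing difficulties with their emotional health". It sets no upper limit on PHQ-9 or GAD-7. It does exclude applicants who are imminently suicidal, but that is not a score limit.

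**The concern.** A threshold set as a percentage of the participant's own baseline asks for more points as the baseline rises. On a scale with a fixed maximum, there is a baseline beyond which the required score does not exist. Participants above that point are counted as not deteriorated whatever happens to them.

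This is a flaw in a rule that the article states in full, with its number. It is not a detail that a fuller plan would be expected to supply.

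Deterioration is the only harm-type outcome for which the article states a between-group comparison, and guided versus unguided delivery is the trial's central contrast. The Introduction says that "participants with severe or complex mental health presentations, such as those with neurological comorbidities including epilepsy, may not achieve good clinical outcomes without clinician support". A reader who wants to know whether unguided delivery leaves some people worse off will look at this rate. Among those most severe at baseline, the rate is fixed at zero by the definition. The severity analyses in section 3.3 cannot recover it if they use the same rule, because a rate fixed at zero stays at zero in the top stratum.

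**Working it through.** The article states no deterioration rate and no power for deterioration, so there is no figure to reproduce. The check is a ceiling calculation.

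**Inputs**
- Relative threshold: 30% (section 3.2).
- Items: 9 and 7 (section 2.7.3). Score ranges are not given. I assume 0-3 per item, so the maximum M is 27 for PHQ-9 and 21 for GAD-7.
- Arms: 150, 150 and 75, in total 375 (section 2.2).
- Baseline distributions: not given, so ranges are assumed below.

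**Who is blocked.** With whole-number scores, the rule can be met from baseline b only if 1.3 × b, rounded up, is no greater than M. That requires b ≤ M/1.3 = 0.769 × M.

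| Scale | M | M/1.3 | Last baseline that can qualify | First blocked baseline | Blocked range |
|---|---|---|---|---|---|
| PHQ-9 | 27 | 20.77 | 20 (1.3 × 20 = 26) | 21 (1.3 × 21 = 27.3, needs 28) | 21-27 |
| GAD-7 | 21 | 16.15 | 16 (1.3 × 16 = 20.8, needs 21) | 17 (1.3 × 17 = 22.1, needs 23) | 17-21 |

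**Dependence on the scoring assumption.** If items scored up to 4, the maxima would be 36 and 28 and the blocked ranges 28-36 and 22-28. The cut-offs move, but a blocked top range remains.

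**How many people.** I used a normal distribution, rounded to whole scores and truncated to the scale, and took the share at or above the first blocked baseline.

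| Scale | Assumed mean | Assumed SD | Share blocked | Per arm of 150 |
|---|---|---|---|---|
| PHQ-9 | 10 | 5 | 1.8% | about 3 |
| PHQ-9 | 12 | 6 | 7.5% | about 11 |
| PHQ-9 | 14 | 6 | 13.0% | about 19 |
| GAD-7 | 8 | 4.5 | 2.9% | about 4 |
| GAD-7 | 10 | 5 | 8.9% | about 13 |
| GAD-7 | 12 | 5.5 | 17.4% | about 26 |

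Wider assumptions (PHQ-9 mean 9-15, SD 5-6; GAD-7 mean 7-13, SD 4.5-5.5) give 1.1%-16.5% and 1.8%-21.6%. Of 375 participants, that is about 4 to 62 and 7 to 81.

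**Effect on the comparison.** Let q be the blocked share, the same in each arm by randomisation, and let p be an arm's deterioration rate among those who can qualify. The reported rate is (1 − q) × p. A difference between arms is likewise multiplied by (1 − q), and a number needed to treat built on it by 1/(1 − q). At q = 0.13 these factors are 0.87 and 1/0.87 = 1.15. At q = 0.174 they are 0.826 and 1/0.826 = 1.21. The comparison is diluted; it is not pushed towards either arm.

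**What a fixed-point rule would do.** A rise of k points is impossible from baselines above M − k. For k = 4, the blocked ranges become PHQ-9 24-27 and GAD-7 18-21. With a PHQ-9 mean of 12 and SD of 6, the blocked share falls from 7.5% to 2.3%. With a GAD-7 mean of 10 and SD of 5, it falls from 8.9% to 5.8%; k = 3 (blocked from 19) would bring it to 3.5%.

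**The case against.** The strongest reply is that worsening in severe participants is not lost. It enters the GEE comparison of PHQ-9 and GAD-7 scores (section 3.1), the severity analyses (section 3.3) and the epilepsy-specific measures NDDI-E and BrEASI (section 2.7.4). A person blocked on one scale may still be classed on the other. Randomisation spreads the blocked group across arms. The outcome is secondary and descriptive. All of this stands and limits the weight of the point. It does not remove it: a mean does not show how many individuals worsened, which is the purpose of a deterioration rate.

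Three stronger readings are tempting, and the article does not support them.

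- **That this is the trial's only harm comparison.** It is the only one the article names. Serious adverse events (section 2.5), seizure frequency (section 2.7.2) and a weekly suicide item (Table 1) are also collected. Their comparison may be set out in a fuller plan.
- **That the rule misses the people most at risk.** The Introduction's concern is that severe or complex cases may not do well, which is lack of benefit rather than worsening, and its wording could cover the whole trial population. Nothing in the article shows that the highest scorers are the likeliest to worsen, and regression to the mean works the other way. What can be said is that the rule misses those most severe at baseline.
- **That the rule loses sensitivity steadily with severity even below the ceiling.** This depends on the model of worsening. If everyone worsens by the same number of points (mean 4, SD 3), simulation of PHQ-9 with a clinical range assumed to start at 10 has the rule flagging about 57% of baselines 10-14 and 37% of 15-19. If worsening is proportional (median factor 1.33, log SD 0.25), it flags about 55% and 54%, and the loss disappears. A relative threshold also fits the log-link models and percentage summaries used elsewhere. Only the zero above the ceiling holds under both models.

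It is also fair to say that choosing relative or absolute change is partly preference, and that a fixed-point rule has a ceiling of its own. That argues for adding such a rule rather than substituting it.

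**Conclusion.** The point holds as a limited one. That the rule cannot be met above about 77% of the maximum is arithmetic and needs no assumption beyond a bounded scale. The cut-offs of 21 (PHQ-9) and 17 (GAD-7) rest on 0-3 item scoring. The shares of roughly 2%-13% and 3%-17% rest wholly on assumed baseline distributions, so they show a plausible size and are not estimates for this trial.

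The consequence is an understated deterioration rate and a diluted between-group comparison, with no information from those most severe at baseline. A reader might go further and infer that a finding of no difference in deterioration would be produced by the definition. That would need the excess worsening to sit mainly in the blocked range, which the article gives no reason to assume. The change is worth making before the analysis because it is cheap.

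**What to change.** In section 3.2, keep the rule of at least 30% so that results remain comparable with earlier trials. Beside it, add a second deterioration criterion: a fixed rise in points for each scale, the same at every baseline, with the post-treatment score in the clinical range. Set the number of points before the data are seen, rather than from the trial's own baseline mean. Compare both criteria between groups, and report by arm how many participants start too high to meet each one.

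The cost is a sentence or two of plan wording and no new data. The downsides are that two deterioration rates are reported, and that the fixed-point rule still leaves some participants out: at 4 points, for example, those starting at PHQ-9 24 or above or GAD-7 18 or above. The counts by arm make that remainder visible.

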### Sensitivity analyses

3.3

Sensitivity analyses will be conducted for primary outcomes based on DSM‐5 diagnostic status and baseline symptom severity. Additionally, we may examine clinically important subgroups based on treatment adherence and any unbalanced or clinically important baseline characteristics.

### Handling missing data

3.4

Following the principle of intention to treat, data from cases that provide baseline data but subsequently do not complete proceeding measures will be handled using a conditional missing at‐random assumption. Consistent with previous research, it is expected that higher baseline symptom severity on the primary outcomes and poorer treatment adherence will increase the likelihood of missing data.^45^, ^46^ Multiple imputations will be used to address missing cases in a conservative manner. This will involve missing outcomes being imputed from pools of participants with similar adherence levels and baseline characteristics (stratified), consistent with previous research.^32^ By employing this strategy, we aim to ensure that imputed data closely align with observed outcomes, enhancing the validity of our analyses.^45^

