The aim of the current study is to assess the comparative effectiveness and acceptability of a digitally delivered psychological intervention aimed at improving both mental health (e.g., depression and anxiety) and functional outcomes (e.g., day‐to‐day disability and perceived cognitive function) of Australian adults with epilepsy. Specifically, this three‐armed RCT will directly compare two clinical care models (guided vs. unguided) of delivering an established digital intervention, the Wellbeing Neuro Course, with a treatment‐as‐usual waitlist control (TAU‐WLC) group.

Consistent with previous trials, we hypothesize that:
Both the guided and unguided groups will result in substantial improvements in primary outcomes of depression and anxiety compared to the TAU‐WLC group.There will be non‐inferiority in clinical efficacy between the guided and unguided groups across the primary outcomes.Both the unguided group and guided group will be cost‐effective compared to TAU‐WLC, but the unguided group will be more cost‐effective relative to the guided group due to lower intervention costs.

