### Power and sample size

2.9

Sample size was determined in line with expert guidelines^43^ and calculations included data from a previous RCT, which observed a standard rate of symptom change on our primary outcomes of depression and anxiety of 24% each.^32^ We utilized specialized longitudinal software^44^ to account for our proposed generalized estimation equations models (GEE). Power analyses were conducted with Type I error set at α = 0.05 and Type II error at β = 80% and utilized a DELTA2 methodology.^43^

Our superiority analyses will compare the two active treatment groups with the TAU‐WLC. We calculated that this requires a sample size of 125:80 (e.g., unguided: control) to detect a difference in the rate of symptom change as small as 11% on the mental health primary outcomes from baseline to post‐treatment.^44^ Our noninferiority analyses will compare the unguided and guided treatment groups. In line with power estimation for non‐inferiority thresholds^44^ in mental health trials,^45^, ^46^ we considered a difference of 50% of the standard rate of symptom reduction in depression and anxiety symptoms (i.e., 12% reduction in symptoms at post‐treatment) as the prespecified margin of noninferiority.^47^ Based on these margins, we require a sample size of 125:125 (unguided: guided).

Utilizing a conservative attrition estimate of 20%, a final larger sample of 150:150:75 (“Guided: Unguided” control) was decided.

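### The stated imputation pools leave out treatment arm, so the method cannot be called conservative for the guided versus unguided non-inferiority comparison

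*Protocol article*

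**What the plan says.** Section 3.4 (Handling missing data) states that cases with baseline data but missing later measures "will be handled using a conditional missing at‐random assumption". It expects that higher baseline severity and "poorer treatment adherence will increase the likelihood of missing data". It then says: "Multiple imputations will be used to address missing cases in a conservative manner", and describes the mechanism: "This will involve missing outcomes being imputed from pools of participants with similar adherence levels and baseline characteristics (stratified". Arm is not named as a pooling variable, and the section does not say that arms are kept apart or merged.

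The second hypothesis in the Introduction is non-inferiority "in clinical efficacy between the guided and unguided groups across the primary outcomes". Section 2.9 sets the margin at half of the 24% reference change, that is "12% reduction in symptoms at post‐treatment".

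Three other places bear on the point. Section 2.2 gives the waitlist the course only at about 6 months. Section 3.1 makes post-treatment the primary endpoint. Section 3.1 also promises efficacy results both with and without imputation.

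**The concern.** Adherence and baseline characteristics do not identify the arm. Baseline characteristics are balanced by randomization, so pooling on them cannot stand in for arm. Adherence can do so only as far as it carries the effect of guidance. Under the rule as worded, a missing unguided outcome may be filled from a guided completer of similar adherence, and the reverse. The two arm means then move toward each other.

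For a superiority comparison, that dilution works against the claim. For non-inferiority it works in favour of the claim, because a smaller estimated deficit lies further inside the margin. The unqualified description of the method as conservative therefore does not carry over to the second hypothesis, which informs the choice between the two care models.

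The waitlist raises a separate difficulty. At post-treatment its members have not been offered any lessons, so course adherence is not defined for them. If they are coded as non-adherent, they share a pool with treated participants who did not use the course.

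**Working it through.** **Inputs from the protocol.** Margin 12 points; 125:125 required and 150:150 randomized to the active arms; 20% attrition (section 2.9). Attrition of 4% in an earlier guided open trial and above 25% in earlier unguided trials (Introduction). Error rates: "Type I error set at α = 0.05 and Type II error at β = 80"%, read here as 80% power. The number of sides is not stated for non-inferiority.

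**The plan's own figure.** No SD or GEE correlation is given, so 125:125 cannot be reproduced independently. Solving n = 2·SD²·(z_alpha + z_power)² / margin² for SD gives:

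- one-sided 0.025: SD = 12 × √(125/2) / (1.960 + 0.842) = 33.9 points
- one-sided 0.05: SD = 12 × √(125/2) / (1.645 + 0.842) = 38.2 points

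**Attenuation when donors are shared and adherence carries none of the arm effect.** Let D be the true difference, m_G and m_U the missing fractions, and p the guided share of observed donors. The expected difference after imputation is

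D × [1 − m_U·p − m_G·(1 − p)]

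- 20% / 20%: p = 120/240 = 0.50, giving 12 × (1 − 0.10 − 0.10) = 9.6
- 4% / 25%: p = 144/(144 + 112.5) = 0.561, giving 12 × (1 − 0.140 − 0.018) = 10.1

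**Error rate at the margin.** Each scenario used 3,000 simulated trials with 150 per arm, a true difference of 12, approximate Bayesian bootstrap imputation (20 imputations) and Rubin's rules.

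Assumptions not in the protocol:
- Outcomes are normal on the percent-change scale.
- Adherence is binary, 80% high in the guided arm, and high adherence is worth 20 points.
- Low adherers are twice as likely to be missing.
- Residual SD is 32.9 or 37.3, so that the total SD matches the values above.
- Pools use adherence only.

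High adherence in the unguided arm was 80%, 50% or 20%. Adherence then carries none, half (20 × 0.30 = 6 points) or all (20 × 0.60 = 12 points) of the difference.

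| Missing G/U | Nominal | Carried by adherence | Estimate, within arm | Estimate, shared | False NI, within arm | False NI, shared |
|---|---|---|---|---|---|---|
| 20/20 | 2.5% | none | 11.96 | 9.60 | 2.7% | 4.2% |
| 4/25 | 2.5% | none | 12.07 | 10.14 | 3.1% | 4.9% |
| 20/20 | 5% | none | 12.05 | 9.61 | 5.3% | 8.2% |
| 4/25 | 5% | none | 12.09 | 10.10 | 5.0% | 7.0% |
| 20/20 | 2.5% | half | 12.07 | 10.95 | 2.6% | 2.2% |
| 20/20 | 2.5% | all | 11.98 | 12.05 | 2.3% | 1.8% |

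The Monte Carlo standard error is about 0.3 to 0.5 percentage points. In the last row the estimate is unbiased but the error rate is below nominal. This is consistent with Rubin's variance being too large when donors are shared, which would also offset the bias in the half-carried case.

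**Waitlist.** No arithmetic applies. Crossover at about 6 months comes after the post-treatment assessment of the 10-week course, so the pooling variable has no defined value at the primary endpoint.

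**The case against.** The strongest reply is that the text is silent rather than wrong. A reader might infer that the protocol rules out imputing by arm. It does not: it neither excludes arm nor says that arms are merged, it does not list the stratifiers in full, and it refers to earlier work for the method. A condensed article may leave the complete imputation model to a plan not shown here. That limits the claim to the rule as worded. It does not remove the claim, because the article names what defines the pools and attaches an unqualified justification to them.

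A reader might also infer that false non-inferiority is inflated whatever happens. That is not supported. The Introduction links level of guidance to engagement, so adherence may carry much of the arm effect, and adherence is already a pooling variable. With half of the effect carried that way there was bias but no inflation; with all of it carried there was no bias. On the other side, section 2.6 has clinicians answering questions, encouraging practice and normalizing difficulties. The Introduction also doubts that complex cases do well without support. An effect beyond adherence is therefore plausible, but its size is unknown.

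The results without imputation have no cross-arm donors and would help expose the effect of pooling. This is a partial check only. The article does not say which analysis decides, it describes imputation as its intention-to-treat approach, and it expects missingness to depend on severity and adherence.

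Finally, it is tempting to say that the weekly PHQ-2 and GAD-2 scores are ignored. The article does not list every imputation variable, so that cannot be concluded.

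**Conclusion.** The point holds in a conditional form. The stated pools omit arm. If they are applied as written and arm acts beyond adherence, a true 12-point difference is estimated at about 9.6 (20% missing per arm) or 10.1 (4% and 25%). At an assumed one-sided 0.025, false non-inferiority goes from about 2.5-3% to about 4-5%; at one-sided 0.05, from about 5% to 7-8%. The error rates rest on a back-solved SD and the simulation assumptions above, and they do not apply if adherence carries half or more of the arm effect. The attenuation formula needs no SD, only that adherence carries none of the effect.

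Calling the method conservative is defensible at most for superiority. The lack of a clear adherence value for the waitlist stands whichever way the silence about arm is read.

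**What to change.** Amend section 3.4, or state in the analysis plan, that:

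- imputation is done within arm, or the imputation model includes arm;
- course adherence is a pooling variable in the two active arms only;
- waitlist outcomes are imputed from waitlist participants;
- the method is not described as conservative for the non-inferiority comparison.

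It should also say whether the imputed or the non-imputed analysis decides non-inferiority.

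The cost is a few sentences and modest programming, with no new data collection. The drawback is smaller donor pools, above all in the waitlist arm of 75; a model that includes arm eases this. If the full plan already imputes within arm, one sentence settles that part.

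A delta-adjusted sensitivity analysis that worsens imputed unguided outcomes, and the use of the weekly PHQ-2 and GAD-2 scores as predictors, would be useful. They are optional additions and do not correct an error.

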### Measures

2.7

A timeline of administration for the measures used is summarized in Table 1.

**TABLE 1 epi412913-tbl-0001:** Timeline for administration of measures.

Measure	Assessment	Pre‐treatment (baseline)	Weekly during treatment	Post‐treatment (10‐week treatment)	3‐month follow‐up	12‐month follow‐up
Participant measure						
Demographics	X					
QuickSCID‐5	X					
Condition details	X					
PHQ‐9	X	X		X	X	X
PHQ‐2			X			
GAD‐7	X	X		X	X	X
GAD‐2			X			
WHODAS 2.0	X	X		X	X	X
NDDIE	X	X		X	X	X
NDDIE‐suicide item			X			
BrEASI	X	X		X	X	X
NeurQol_Cognitive function		X		X	X	X
Seizure frequency	X	X	X	X	X	X
CCSQ		X		X	X	X
TSQ				X		
ReQOL‐10		X		X	X	
EQ‐5D‐5L		X		X	X	
Use of care services (purpose‐built based on the iMTA TIC‐P)		X		X	X	

Abbreviations: BrEASI, Brief Epilepsy Anxiety Instrument; CCSQ, Compensatory Cognitive Strategies Questionnaire; GAD‐7, Generalized Anxiety Disorder – 7; iMTA, Institute for Medical Technology Assessment; NDDI‐E, Neurological Depressive Disorder Inventory‐Epilepsy; PHQ‐9, Patient Health Questionnaire‐9; QuickSCID‐5, Quick Structured Clinical Interview for DSM‐5; ReQOL‐10, Recovering Quality of Life 10‐item; TIC‐P, Treatment Inventory of Costs in Patients with Psychiatric Disorders; TSQ, Treatment Satisfaction Questionnaire.

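### The stated imputation basis names adherence and baseline but no on-treatment symptom score, although PHQ-2 and GAD-2 are collected weekly; adding them is a cheap safeguard for the guided–unguided comparison

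*Protocol article*

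**What the plan says.** All references are to the protocol article.

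- **Imputation (Handling missing data, 3.4).** Participants with baseline data but missing later measures are "handled using a conditional missing at‐random assumption". Their missing outcomes are "imputed from pools of participants with similar adherence levels and baseline characteristics (stratified"). The section expects that "higher baseline symptom severity on the primary outcomes and poorer treatment adherence will increase the likelihood of missing data".
- **Data collected (Measures, 2.7, Table 1).** Under the column "Weekly during treatment" the table marks PHQ-2 and GAD-2, the two-item companions of the two primary instruments. No section mentions an analytic use for them.
- **Primary endpoint (Clinical efficacy, 3.1).** This is post-treatment, the assessment that directly follows the weekly series.
- **Dropout.** The Introduction reports that two unguided epilepsy trials "they also experienced relatively high dropout rates (>25"%), while an open trial of a guided intervention "observed very low rates of attrition (4"%). It comments: "These findings highlight potential differences in intervention engagement based on levels of guidance". Power and sample size (2.9) uses a single figure for all arms: "Utilizing a conservative attrition estimate of 20"%.

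**The concern.** A missing-at-random assumption is only as good as the variables it conditions on. Adherence records how much of the course someone did, not whether they were getting better or worse. Take two participants with the same baseline score and the same number of lessons, one improving week by week and the other worsening before leaving. On the stated basis both belong to the same imputation pool. If worsening makes people leave, those who remain in the pool are on average better than those who left, and the imputed values are too favourable.

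This matters most for guided against unguided, because that is the non-inferiority comparison. If more unguided than guided participants leave, more of the favourable values enter the unguided arm, and the error pushes towards the hypothesised conclusion. The checks described would not reveal it. The completers' analysis (Clinical efficacy, 3.1) is exposed to the same selection. The Sensitivity analyses section (3.3) looks at diagnosis, baseline severity and possibly adherence, but does not vary the imputation.

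**Working it through.** **The plan's own figures.** The article gives no number for the imputation itself. Its one missing-data figure, 20% attrition, is not disputed here.

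**Where imputed values would fall.** With 150 per active arm and the Introduction's cited rates (taking 25% for the figure given as above 25%):
- unguided: 150 × 0.75 = 112.5, so about 112 observed and 38 imputed;
- guided: 150 × 0.96 = 144 observed and 6 imputed.

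At a flat 20%, each arm would have 120 observed and 30 imputed.

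**Formula.** Let d be the dropout fraction in an arm and δ the mean imputed minus the mean true score among its leavers, in SD. Higher scores are worse, so a negative δ flatters the arm. Then

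shift (unguided − guided) = 0.25 × δ(unguided) − 0.04 × δ(guided).

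If δ were equal in both arms, the shift would be 0.21 × δ. A shift of 0.03 to 0.09 SD would then mean that leavers' imputed scores are too good by 0.03/0.21 = 0.14 to 0.09/0.21 = 0.43 SD.

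**Simulation.** There were 400,000 participants per arm and no true difference between arms. Variables were multivariate normal: baseline, adherence, last weekly score and post-treatment score. Dropout was logistic and calibrated to 25% and 4%. Missing values were filled by regression on the observed, within arm. All correlations and log-odds below are assumptions; the article gives none.
- Baseline–post and weekly–post correlations: 0.4 and 0.6, or 0.5 and 0.8. Baseline–weekly: 0.55.
- Adherence with weekly and with post: 0 or −0.3.
- Log-odds of dropout per SD of baseline: 0.3 throughout. For adherence and weekly score, see the table.

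| Dropout mechanism (log-odds: adherence, weekly) | Shift, imputing on baseline + adherence | Shift with last weekly score added |
|---|---|---|
| Adherence and baseline only (−0.8, 0) | at most 0.001 SD | at most 0.001 SD |
| Weak symptom effect (−0.8, 0.2) | −0.013 to −0.021 SD | at most 0.001 SD |
| Direct symptom effect (−0.5, 0.5 to 1.0) | −0.029 to −0.094 SD | at most 0.001 SD |

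Rounded, the second column is 0, 0.01–0.02 and 0.03–0.09 SD in favour of the unguided arm.

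**What moves these figures.**
- Equal 20% dropout in both arms, with the strongest direct effect: contrast shift about 0 (0.002 SD).
- Adherence correlated −0.5 with weekly and post scores: the direct-effect range falls to 0.015–0.050 SD.
- Pools that mix the arms (the article does not say which): the direct-effect range is 0.02–0.08 SD.
- The near-zero last column follows by construction, because dropout depends on exactly the score that is added and everyone has it. With a stale score instead (correlation 0.6 with the true last score), only about a quarter to a third of the shift is removed.

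**Against the margin, as a rough guide.** No SD is given. The simple two-mean formula with one-sided 0.025 and 80% power gives n = 2 × (1.96 + 0.84)² × (SD/margin)². Setting n = 125 gives SD/margin = √(125/15.7) = 2.82, so the margin is about 0.354 SD. A shift of 0.03–0.09 SD is then 0.03/0.354 = 8% to 0.09/0.354 = 25% of it, and 0.01–0.02 SD is 3% to 6%. The article used longitudinal software and does not state sidedness, so these shares are only indicative.

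**The case against.** The strongest reply is that this infers an omission from silence. The article never says that pools use only adherence and baseline. It gives one sentence, points to earlier work for the method, and may leave auxiliary variables to an analysis plan that is not shown. That stands as far as it goes: a reader might infer that the weekly scores are discarded, and the document supports only that no use is mentioned. But the article does state the basis of imputation, and an analysis plan that followed it as written would omit the weekly scores. The point is therefore a better choice than the one stated, and not a request for missing detail.

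Second, the article names its own expected mechanism, baseline severity and adherence, and conditions on both. If that account is complete, the shift is zero, as the first table row shows. This stands, and it makes the concern conditional.

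Third, a reader might infer that the plan expects dropout to differ by arm. It does not. The Introduction says potential, its two rates come from separate trials, one of them uncontrolled, and the sample size assumes 20% overall. With equal dropout and the same causes in both arms, the contrast is unaffected.

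Fourth, the remedy is easily oversold. Early leavers have few weekly scores, and the article does not say whether the waiting-list arm completes the weekly forms. This also stands.

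**Conclusion.** The concern holds as a conditional weakness in the stated method, not as an error or contradiction in the protocol. The stated imputation basis leaves out scores that are already collected, sit closest in time to the primary endpoint, and plausibly predict both leaving and outcome. The guided–unguided comparison shifts towards non-inferiority only if two things are true: dropout depends on symptom course beyond baseline and adherence, and dropout is higher in the unguided arm. With 25% against 4% dropout, the size is about 0 if dropout follows adherence only, 0.01–0.02 SD with a weak symptom effect and 0.03–0.09 SD with a direct one. These values rest on assumed correlations and log-odds, and are smaller if adherence tracks symptoms closely.

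Two stronger conclusions are not supported: that the non-inferiority result will be biased, and that weekly scores would eliminate any bias. The article is also silent on whether a participant's own post-treatment score informs the imputation of later values. That is a secondary matter, since follow-up is examined as within-group maintenance and does not bear on the primary endpoint.

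**What to change.** Keep adherence and baseline characteristics in the imputation. Add the last available PHQ-2 and GAD-2 when imputing post-treatment PHQ-9 and GAD-7 in the two active arms, and in the waiting-list arm if it completes the weekly forms. As a secondary step, include observed earlier PHQ-9 and GAD-7 scores when imputing the 3- and 12-month values.

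The cost is a few more variables in the imputation model, settled before analysis, with no new data or assessments. The downsides are modest. Weekly scores will themselves be incomplete, so early leavers gain less and bias is reduced rather than removed. If the waiting-list arm has no weekly scores, its imputation model will differ from that of the active arms, and this should be stated when the superiority comparisons are reported.
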